### Study activities and procedures

Written informed consent for participation in the study will be obtained before performing any study-specific procedures. Paired samples (fingerstick blood sample and venous blood sample in non-anticoagulated tube) will be collected at the time of enrolment and follow-up visits, where venous blood samples will be tested at the Southwest London Pathology Laboratory situated at Kingston NHS Hospital. The samples will be used for the sFlt/PlGF test with the Roche assay as is routine for participating hospitals, and an aliquot of the sample will be stored at −18 °C for future testing for serum PlGF using the POC plasma PlGF (Quidel) test retrospectively.

### Primary and secondary outcomes

The *primary outcome* is delivery for confirmed pre-eclampsia within 4 weeks of testing.

The *secondary outcomes* include diagnosis of pre-eclampsia within 7 and 28 days of sampling, severe gestational hypertension, severe preterm pre-eclampsia, severe maternal complications (cerebrovascular accidents, pulmonary oedema, renal failure or HELLP) and preterm birth.

A composite perinatal mortality/neonatal morbidity score will be assigned based on information captured including survival status at 28 days or discharge (whichever occurs first) and clinical complications including admission to the neonatal intensive care unit, respiratory distress syndrome, bronchopulmonary dysplasia, intraventricular haemorrhage, retinopathy of prematurity, necrotising enterocolitis requiring surgery and days of assisted ventilation.

All outcome data will be collected from hospital records of participants and their newborns.

## Data analysis

### Primary objective analysis

The primary analysis will be based on the cross-tabulation of the binary outcome variable, delivery for pre-eclampsia within 4 weeks of the sflt/PlGF ratio testing result versus the GlyFn (Lumella) test result. As stated, the GlyFn test results will be dichotomised into low risk/high risk based on thresholds derived from our study cohort. Sensitivity and specificity will be computed from this cross-tabulation, along with 95% CIs, which will be computed simultaneously via methods outlined by Pepe.^30^ In addition, a concordance index (C index) will be computed to measure the overall discrimination performance.^31^

To assess whether the difference between the POC GlyFn and sFLT/PlGF-based tests is statistically significant, a fixed-effects logistic regression model will be constructed given the multilevel data structure. A fixed-effects model has the advantage of taking into account any individual-level risk factors including un-observed risk factors. OR, its associated p value and 95% CI will be reported. We will also report the diagnostic performance of the POC plasma PlGF (Quidel) test for the same primary outcome.

### Secondary/subgroup analyses

Secondary analysis will estimate the positive and negative predictive values (PPV and NPV, respectively) for the detection of pre-eclampsia within 4 weeks of sampling for the POC GlyFn test, sFLT/PlGF ratio and POC plasma PlGF (Quidel) test. The PPV and NPV, along with the 95% confidence rectangle (ie, CIs for each metric estimated jointly), will be computed under various pre-eclampsia prevalence assumptions, including the prevalence observed in the current study, as well as lower/higher estimates reported in the literature. The optimum cut-off value of the Lumella test will be determined for testing the non-inferiority hypothesis for the sensitivity to the primary outcome (delivery for pre-eclampsia within 4 weeks of the first test).

Furthermore, secondary analyses will be conducted by substituting (a) pre-eclampsia within 2 weeks of sampling, (b) development of pre-eclampsia with severe features (yes/no), and (c) preterm delivery (yes/no) into the cross-tabulation instead of pre-eclampsia (yes/no).

In addition, the time to development of PE and time to delivery for subjects with low-risk and high-risk results (based on the derived test cut-off) will be assessed using Kaplan-Meier curves and Cox proportional hazards models. All analyses will be re-performed based only on certain prespecified subgroups, such as women with chronic hypertension at baseline, gestational age (<34 or ≥34 weeks), interventions and presence of gestational diabetes.

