### Inclusion and exclusion criteria

Potential participants are those with a gestational age between 24^+0^ and 36^+6^ if they are aged 18 or over with plans to deliver at the study site. The exclusion criteria are as follows: diagnosis of pre-eclampsia at the time of enrolment, planned delivery prior to 37^+0^ weeks for other clinical reasons or pregnancies with known/suspected major fetal structural or chromosomal abnormality.

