### Sample size calculation

A total of 400 participants will be recruited across the study sites. Sample size of the cohort was estimated using a formula described by Alonzo *et al*^28^ for demonstrating the non-inferiority of the POC GlyFn test (Lumella) compared with PIGF and sFlt/PIGF for pre-eclampsia prediction, with sensitivity as the primary endpoint at a non-inferiority margin of 5%. The prevalence of pre-eclampsia in this high-risk population was estimated to be 23% according to data from the INSPIRE study.^29^

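### Kaplan-Meier curves for time to pre-eclampsia overstate absolute risk if women are censored at delivery without pre-eclampsia; cumulative incidence curves should replace them

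*Protocol article*

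**What the plan says.** In the protocol article, Data analysis, Secondary/subgroup analyses, two time-to-event endpoints are named: "the time to development of PE and time to delivery for subjects with low-risk and high-risk results". Both "will be assessed using Kaplan-Meier curves and Cox proportional hazards models". The same section says that all analyses are repeated in subgroups, which include "gestational age (<34 or ≥34 weeks), interventions and presence of gestational diabetes".

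Three other places matter:

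- Inclusion and exclusion criteria: women enter at a "gestational age between 24^+0^ and 36^+6" weeks.
- Sample size calculation: "The prevalence of pre-eclampsia in this high-risk population was estimated to be 23" per cent, with 400 women to be recruited.
- Table 2, key secondary outcomes: pre-eclampsia diagnosed later, up to the postpartum period, is also collected.

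For these curves the article names no competing event, censoring rule or time horizon.

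**The concern.** Kaplan-Meier has one event type and treats everyone else as censored. For time to any delivery that is adequate, because every woman delivers. For time to pre-eclampsia, delivery without the condition is a second way of leaving the risk set, and it is the usual one here. Censoring at delivery treats these women as if they stayed pregnant, at the same risk as women who are still pregnant. One minus the curve then describes a population in which nobody delivers for any other reason.

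The curves are to be drawn by low-risk and high-risk Lumella result, so they invite reading as the absolute risk of pre-eclampsia after each result. They could also disagree with the article's own predictive values. Those count a woman who delivered without pre-eclampsia within 4 weeks as a non-event, whereas a curve that censors her would show a higher 4-week risk for the same result group.

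**Working it through.** The article gives no figure for this analysis, so there is none to reproduce. The check uses its 23% and 400, its entry window, and assumed timings.

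**How common the competing event is.** If 23% is read as the share who develop pre-eclampsia during follow-up, 400 × 0.23 = 92 women have the event and 400 × 0.77 = 308 deliver without it.

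**Direction.** At each time, both estimators add the pre-eclampsia hazard multiplied by a survival term. Kaplan-Meier uses survival from pre-eclampsia alone. Aalen-Johansen uses survival from both events, which cannot be larger. With censoring at delivery, one minus Kaplan-Meier (1 − KM) can therefore never be below the cumulative incidence.

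**Size, analytic.** Let p be the true cumulative incidence and c the share delivered without pre-eclampsia, with proportional cause-specific hazards. Then

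1 − KM = 1 − (1 − p − c)^(p/(p + c)).

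For p = 0.23 and c = 0.50: 1 − 0.27^(0.23/0.73) = 1 − 0.27^0.315 = 0.338.

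| Delivered without pre-eclampsia (c) | True risk | 1 − KM |
|---|---|---|
| 10% | 23% | 24.4% |
| 30% | 23% | 27.9% |
| 50% | 23% | 33.8% |
| 70% | 23% | 48.2% |

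**Size on a time axis, by simulation.** The assumptions, none from the article, are:

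- entry spread uniformly over the gestational range shown;
- delivery around 39 weeks with SD 1.5, always after entry and no later than 42 weeks;
- 23% developing pre-eclampsia in every entry group;
- onset either evenly spread between entry and delivery or weighted towards delivery.

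| Entry group | Delivered without pre-eclampsia by 28 days | Onset | Cumulative incidence, 28 days | 1 − KM, 28 days | 1 − KM, end |
|---|---|---|---|---|---|
| All | 12% | even | 12.8% | 13.3% | 36.1% |
| All | 12% | late | 8.7% | 9.2% | 43.1% |
| Before 34 weeks | 2% | even | 10.5% | 10.5% | 33.3% |
| Before 34 weeks | 2% | late | 5.4% | 5.5% | 39.3% |
| 34 weeks or later | 47% | even | 21.1% | 25.2% | 36.4% |
| 34 weeks or later | 47% | late | 19.7% | 25.0% | 43.1% |

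The true value at the end is 23% in every row. The 28-day excess is about 0.5 points overall (13.3 − 12.8; 9.2 − 8.7) and 0.1 or less before 34 weeks. At 34 weeks or later it is 4.1 to 5.3 points (25.2 − 21.1; 25.0 − 19.7).

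**By result group, to the end of follow-up.** With an assumed true risk of 10% in a low-risk group, 1 − KM reads 16.3% to 20.4%. With an assumed 60% in a high-risk group, it reads 81% to 88%.

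**The case against.** The strongest reply is that the article never says women are censored at delivery. If women who deliver without pre-eclampsia stay in the risk set to a fixed horizon, the bias disappears. Table 2 makes that conceivable, since pre-eclampsia is recorded into the postpartum period and delivery does not end ascertainment. A condensed article may also leave censoring rules to a fuller document. This stands as a limit: the overstatement is conditional on censoring at delivery. It does not remove the point, because the article does fix Kaplan-Meier for an endpoint that most women never reach, and censoring at delivery is its ordinary use.

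The second reply concerns size. The study's named windows are 7 days, 2 weeks and 4 weeks, and over these the overall excess is small. That also stands, except for entry at 34 weeks or later. Absolute risk at 4 weeks is moreover available from the predictive values, which are simple proportions.

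A reader might infer more than the documents support:

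- **That the plotted risks are bound to be too high, or about double.** No censoring rule is stated. A doubling (for example 41.1% against 20.7%) arises under proportional hazards when 90% of women have had one event or the other, and the article does not say that the curves run that far.
- **That the distortion is known to differ between result groups because clinicians see the sFlt/PlGF result.** This is plausible, and the article itself lists intervention bias as a limitation. But it gives nothing from which to size the effect, and the simulation used the same delivery timing in both groups.
- **That the Cox model is invalid.** With censoring at delivery it estimates a cause-specific hazard ratio, which is interpretable if labelled as such.

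**Conclusion.** The point holds in conditional form. Kaplan-Meier is a poor choice for time to pre-eclampsia when about 77% of women are expected to deliver without it. If they are censored at delivery, the direction of the error is certain. Its size rests on assumed delivery and onset timing and on reading the 23% prevalence as the share who develop the condition. It is negligible to small at 28 days overall, material at 28 days for entry at 34 weeks or later, and large only if curves continue to delivery.

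This is a minor-to-moderate matter in a secondary analysis. The primary sensitivity comparison, the predictive values and the time-to-delivery analysis are not affected.

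**What to change.** For time to pre-eclampsia, overall and in the subgroups, replace the Kaplan-Meier curves with Aalen-Johansen cumulative incidence curves, with delivery without pre-eclampsia as the competing event. State the time horizon.

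Define how postpartum pre-eclampsia is counted, because a competing event defined simply as delivery would drop those cases. Two workable choices are:

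- end the antenatal curve at delivery and report postpartum pre-eclampsia separately; or
- define the competing event as delivery with no pre-eclampsia by the end of postpartum ascertainment, which requires that ascertainment to be complete.

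Keep the Cox model for time to pre-eclampsia, but label its result a cause-specific hazard ratio. Keep Kaplan-Meier for time to any delivery.

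The cost is small: the same data, a standard routine, a little more analysis work, a decision on postpartum cases, and lower risk figures than Kaplan-Meier would show. With complete follow-up, the curve read at 4 weeks would then agree with the cross-tabulated risk in each result group at the observed prevalence, provided both count pre-eclampsia in the same way.

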An important supplement to diagnoses based on observable clinical presentation is the determination of the levels of specific biomarkers that can be measured in body fluids such as blood or urine. Several circulating factors are associated with pre-eclampsia, including soluble endoglin, placental growth factor (PlGF), soluble fms-like tyrosine kinase-1 (sFlt-1), vascular endothelial growth factor, pregnancy-associated plasma protein A-2, vasopressin, copeptin and glycosylated fibronectin (GlyFn).^17^,^21^ Although many of the above markers have shown changes in pregnancies affected by pre-eclampsia prior to onset and after the detectable onset of the condition, only some have been validated for routine clinical use to assess pre-eclampsia. A high serum level of maternal GlyFn is proposed as a highly sensitive and specific biomarker for pre-eclampsia, making it a useful adjunct diagnostic test in the evaluation of new-onset hypertension in pregnancy.^1722^,^25^ The availability as a point of care (POC) test makes it suitable for use, particularly for triage and in high-resource and low-resource settings. The Lumella GlyFn test uses a maternal finger-stick blood sample to determine the levels of a specific glycosylated form of fibronectin as a biomarker for pre-eclampsia. It has been proposed as an alternative to the sFlt-1/PlGF ratio for the assessment of the risk of developing pre-eclampsia within 2 and 4 weeks of testing.^26^ The majority of evidence for the utility of the glycosylated fibronectin test is based on retrospective studies using stored samples.

This clinical study will prospectively evaluate the quantitative POC measurement of GlyFn in maternal blood. The test will be used as an aid in the risk assessment of women with clinical findings suggestive of pre-eclampsia, in conjunction with other clinical and laboratory information. This study is designed to bridge the current gap in evidence around the effectiveness of POC GlyFn testing in the diagnosis and clinical triage for pre-eclampsia and compare performance against the current standard of care. The availability of such tests can have an impact on reducing maternal and neonatal risks associated with severe pre-eclampsia.

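### The Cox models for time to pre-eclampsia and time to delivery are described only by low/high GlyFn group; a continuous-GlyFn model should be added beside them, mainly for the subgroups.

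*Protocol article*

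**What the plan says.** The Introduction presents GlyFn as a measured quantity: "This clinical study will prospectively evaluate the quantitative POC measurement of GlyFn in maternal blood". Under Primary objective analysis, "the GlyFn test results will be dichotomised into low risk/high risk based on thresholds derived from our study cohort". No GlyFn value and no expected share of high-risk women is given.

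Secondary/subgroup analyses carries that grouping into the time-to-event work: outcomes for women with "low-risk and high-risk results (based on the derived test cut-off) will be assessed using Kaplan-Meier curves and Cox proportional hazards models". The same section adds: "All analyses will be re-performed based only on certain prespecified subgroups, such as women with chronic hypertension at baseline". Gestational age, interventions and gestational diabetes are the other subgroups named, without sizes.

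Primary objective analysis also plans that "a concordance index (C index) will be computed to measure the overall discrimination performance", but does not say whether the C index uses the measured value or the two-way result. The article describes no Cox model with GlyFn as a continuous covariate.

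**The concern.** Sensitivity, specificity and predictive values need a two-way test result. A Cox model does not. Splitting a quantitative marker treats all women on one side of the cut-off as having the same risk, and the model cannot show how risk changes across the GlyFn range. The cut-off is to be chosen for the sensitivity comparison on delivery for pre-eclampsia within 4 weeks, not to describe the hazard.

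At stake is the precision of the secondary hazard ratios, above all in the subgroups, where events are few. The primary sensitivity comparison is not affected.

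**Working it through.** The article gives no figure for the Cox models, so there is none to reproduce. It supplies only the event count.

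**Inputs from the article**
- Size: "A total of 400 participants will be recruited across the study sites".
- Pre-eclampsia prevalence: "estimated to be 23% according to data from the INSPIRE study".
- Expected events: 400 × 0.23 = 92.

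**Assumptions (not in the article)**
- GlyFn is normal on a suitable scale and the log-hazard is linear in it.
- The share classed high risk, *q*, lies between 23% and 50%.
- A subgroup holds 20% of the cohort: 80 women and 80 × 0.23 = 18.4 events.
- The hazard ratio (HR) per SD is shown over a range.

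**Step 1. Information kept by the split.** Relative efficiency = φ(z)² / [q(1 − q)], where z is the normal quantile at 1 − q.

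| q | Kept | Lost |
|---|---|---|
| 50% | 0.64 | 36% |
| 35% | 0.60 | 40% |
| 23% | 0.52 | 48% |
| 10% | 0.34 | 66% |

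The formula is for a weak effect. Cox simulations with 400 women, 23% events and HR 1.5 to 3 per SD (60 runs per setting) gave losses of 34% to 44% for shares of 23% to 50%.

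**Step 2. Power.** Power = Φ(√(events × efficiency) × ln HR − 1.96), with efficiency 1 for the continuous model.

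| Events | HR per SD | Continuous | Two groups (q = 23% / 35% / 50%) |
|---|---|---|---|
| 18 | 2.0 | 84% | 56% / 63% / 65% |
| 18 | 2.5 | 97% | 80% / 86% / 87% |
| 92 | 1.5 | 97% | 80% / 86% / 87% |
| 92 | 2.0 | about 100% | about 100% |

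For example, √18 × ln 2 = 2.94, and Φ(2.94 − 1.96) = 0.84. With q = 23%, 2.94 × √0.52 = 2.12, and Φ(2.12 − 1.96) = 0.56. A Cox simulation of 80 women at HR 2.0 and a 35% share gave about 81% v 63%, in line with the formula.

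**Step 3. If risk steps at the cut-off.** Simulating a hazard that jumps exactly there, the two-group model had a likelihood-ratio statistic 55% to 73% larger than the linear continuous model. The loss in Step 1 then does not occur.

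**Step 4. Can the low-risk group hold no pre-eclampsia events?** P(none) = sensitivity^events. With 18.4 events, sensitivity of 0.90 or 0.95 gives 14% or 39%; 0.80 gives 2%. In a subgroup of half the cohort (46 events), 0.90 or 0.95 gives 1% or 9%.

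Those sensitivities do not go with the hazard ratios in Step 2. Under the same normal, linear model with 23% events, the implied sensitivity at shares of 23% / 35% / 50% is:
- HR 2.0: 0.43 / 0.58 / 0.72
- HR 2.5: 0.49 / 0.64 / 0.78

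Expected low-risk events are then 18.4 × (1 − 0.78) = 4.0 up to 18.4 × (1 − 0.43) = 10.5, and P(none) is about 1% or less. At HR 5 with a median split, sensitivity is 0.89 and P(none) is 12%.

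For time to delivery the question does not arise, because every woman followed up delivers.

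**The case against.** The strongest defence is that the grouping matches the stated question: how long until pre-eclampsia or delivery for women with a low-risk or high-risk result, as the test would be reported. A high v low hazard ratio answers that and an HR per SD does not. This stands, and it is why the grouped model should be kept.

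A second objection is that the size of the loss rests on assumptions that the article does not make, and that a step in risk at the cut-off would favour two groups. This also stands, so the percentages are conditional. The article gives no reason to expect a step at a value picked from the sample, though it does not rule one out.

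A third is that the form of a covariate in a secondary model can be left to an analysis plan that is not shown. This stands only in part. The article does not exclude a continuous model, but it does name a specific grouped analysis, and the comment is on that choice.

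A reader might go further and infer that subgroup hazard ratios will often be infinite because a cut-off chosen for sensitivity leaves almost no low-risk events. The article does not support this. The cut-off is tuned to delivery for pre-eclampsia within 4 weeks, whereas the Cox endpoint is development of pre-eclampsia with no such limit stated, so later cases in low-risk women count as events. Subgroup sizes are not given. The large power loss and the empty low-risk group also need different marker strengths, as Step 4 shows.

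**Conclusion.** The point holds as a modest improvement to a secondary analysis. The article describes the Cox models only by risk group for a marker that it calls quantitative. With a roughly normal marker, a linear log-hazard and 23% to 50% of women high risk, the loss is about 36% to 48% of the information. It is larger at a more extreme share and absent if risk steps at the cut-off.

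The consequence is mainly in subgroups: about 20 to 30 points of power with 18 events at HR 2.0 per SD, and 10 to 17 points at 2.5. In the whole cohort the gap is 10 to 17 points at HR 1.5 per SD and negligible at 2.0 or more. A sparse or empty low-risk group is a possibility only for time to pre-eclampsia, in small subgroups with a very strong marker.

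It would be wrong to conclude that the grouped model is an error, that the loss is a known quantity, or that the article contradicts itself here.

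**What to change.** Keep the Kaplan-Meier curves and the grouped Cox model as the description of the test as used. Beside them, state that a Cox model will enter log GlyFn as a continuous covariate, as a restricted cubic spline in the whole cohort and as a linear term in the subgroups, with the hazard ratio per SD or per doubling. Fit the same model for the log sFlt/PlGF ratio, with per-SD hazard ratios to put the two tests on a common scale. Name the continuous model as the main estimate in the subgroups.

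This costs a sentence or two of analysis wording and minor programming, with no new data. It is best settled before the cut-off is derived. The downside is one more model to report and a hazard ratio that is less direct to read than high v low risk.

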**Methods and analysis:**

This is a multicentre prospective study. Women at risk for pre-eclampsia based on predefined clinical and/or obstetric risk factors will be invited to participate in the study. The recruitment target is 400 participants. Consenting participants will have paired samples for sFlt/PlGF together with POC GlyFn testing. Two follow-up visits are planned at 2 and 4 weeks after the initial recruitment where repeat testing with both tests will be performed. The clinical team will be blinded to the results of the GlyFn test but not that of the sFlt/PlGF test. Clinical care will be based on established protocols incorporating maternal/fetal evaluation and the results of sFlt/PlGF levels. Maternal and neonatal outcome data will be collected to compare the sensitivity and specificity of the tests, with the primary outcome being delivery for pre-eclampsia within 4 weeks.

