**Trial registration number:**

ISRCTN13430018

STRENGTHS AND LIMITATIONS OF THIS STUDYThis diagnostic test accuracy study used a paired design for the head-to-head comparison with the current gold standard test.The results of the Lumella test will be unknown to the clinical team and will not influence decision making.The clinical team will have the results of placental growth factor-based testing if available, which may introduce intervention bias.

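### The undated interventions subgroup may stratify on care that follows the disclosed sFlt/PlGF result, which can make two equally accurate tests look different

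*Protocol article*

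**What the plan says.** The Secondary/subgroup analyses section of the protocol article states: "All analyses will be re-performed based only on certain prespecified subgroups, such as women with chronic hypertension at baseline". The list continues with gestational age below or from 34 weeks, and ends with "interventions and presence of gestational diabetes". Interventions are not defined or dated anywhere in the article.

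Three other statements bear on what the word could cover:

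- Abstract, Methods and analysis, on blinding: "The clinical team will be blinded to the results of the GlyFn test but not that of the sFlt/PlGF test".
- The same paragraph, on care: "Clinical care will be based on established protocols incorporating maternal/fetal evaluation and the results of sFlt/PlGF levels".
- Strengths and limitations: "The results of the Lumella test will be unknown to the clinical team and will not influence decision making", followed by "The clinical team will have the results of placental growth factor-based testing if available, which may introduce intervention bias".

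The study is described as observational (Recruitment and sampling). Paired testing is repeated at 2 and 4 weeks. The primary outcome is delivery for confirmed pre-eclampsia within 4 weeks, and the non-inferiority margin for sensitivity is 5% (Sample size calculation).

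**The concern.** An observational study assigns no intervention, so the word must refer to clinical care. Some of that care may follow the first paired sample, and the article says that care takes account of the ratio but not of GlyFn. If such care defines the subgroup, membership is partly an effect of the ratio result.

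The treated stratum is then enriched for ratio-positive women and the untreated stratum for ratio-negative women. The ratio's sensitivity rises and its specificity falls in the first; the reverse happens in the second. GlyFn moves only as far as it is correlated with the ratio. A reader of the subgroup tables could conclude that GlyFn is worse in treated women and better in untreated women when selection alone produced the pattern. Because all analyses are to be repeated, the non-inferiority comparison of sensitivity is among those exposed.

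**Working it through.** The article gives no figure for this subgroup, so there is nothing to reproduce. The check asks what two equally accurate tests would show.

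**Inputs from the article.** Margin 5%; 400 women; pre-eclampsia prevalence 23%, so 0.23 × 400 = 92 cases. This is a generous count for the primary outcome, which is narrower (delivery for pre-eclampsia within 4 weeks).

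**Assumptions (not in the article).** Both tests have sensitivity s = 0.85. Among cases, the probability of intervention is p₁ if the ratio is positive and p₀ if it is negative, and depends on nothing else. The two results have within-case correlation ρ.

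**Formulas.**

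- Ratio sensitivity in treated cases: p₁s / [p₁s + p₀(1−s)].
- Ratio sensitivity in untreated cases: (1−p₁)s / [(1−p₁)s + (1−p₀)(1−s)].
- GlyFn sensitivity in a stratum: s + ρ × (ratio sensitivity in that stratum − s).
- False difference, GlyFn minus ratio: (1−ρ) × (s − ratio sensitivity in that stratum).

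**Strong steering, p₁ = 0.7, p₀ = 0.2.** Treated: 0.595 / (0.595 + 0.030) = 0.952. Untreated: 0.255 / (0.255 + 0.120) = 0.680.

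**Weak steering, p₁ = 0.4, p₀ = 0.3.** Treated: 0.340 / (0.340 + 0.045) = 0.883. Untreated: 0.510 / (0.510 + 0.105) = 0.829.

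| Steering | ρ | Treated: ratio / GlyFn | Difference | Untreated: ratio / GlyFn | Difference |
|---|---|---|---|---|---|
| 70% vs 20% | 0 | 95.2 / 85.0 | −10.2 | 68.0 / 85.0 | +17.0 |
| 70% vs 20% | 0.5 | 95.2 / 90.1 | −5.1 | 68.0 / 76.5 | +8.5 |
| 40% vs 30% | 0 | 88.3 / 85.0 | −3.3 | 82.9 / 85.0 | +2.1 |
| 40% vs 30% | 0.5 | 88.3 / 86.7 | −1.7 | 82.9 / 84.0 | +1.0 |
| 40% vs 40% | any | 85.0 / 85.0 | 0 | 85.0 / 85.0 | 0 |

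Sensitivities are in per cent and differences in percentage points, taken before rounding.

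**Wider grid.** With sensitivity 0.80 to 0.90, steering from 40/30 to 80/10 and ρ from 0 to 0.6, the false difference runs from −0.9 to −17.0 points in treated cases and from +0.6 to +32.9 in untreated cases.

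**Specificity moves too.** Take specificity 0.80, steering 70/20 and ρ = 0.3. In treated non-cases the ratio shows 0.16 / (0.16 + 0.14) = 53.3%, and GlyFn 0.80 + 0.3 × (0.533 − 0.80) = 72.0%. In untreated non-cases the ratio shows 0.64 / (0.64 + 0.06) = 91.4%, and GlyFn 0.80 + 0.3 × (0.914 − 0.80) = 83.4%.

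**Scale against the case count.** Strong steering puts 0.625 × 92 ≈ 58 cases in the treated stratum and 34 in the untreated, so false differences of 10.2 and 17.0 points correspond to about six cases in each. Weak steering puts about 35 and 57 cases there, and the false differences at ρ = 0.5 amount to less than one case in each.

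**The case against.** The strongest reply is that the harmful reading is inferred from one undefined word. Women can enter with pre-existing hypertension, diabetes or renal disease, so treatment already in place at the first sample is a possible meaning, and the other listed subgroups are patient characteristics. The baseline tag on chronic hypertension proves little, because gestational age lacks it too and would ordinarily be read as age at testing. The remark on intervention bias is a general limitation and is not tied to this subgroup. The list is illustrative, and exact definitions may stand in the full protocol or analysis plan. All of this stands. A reader might infer that the plan certainly conditions on post-test care; the article does not say so.

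The size is also open to challenge. Care incorporates maternal and fetal evaluation as well as the ratio; the article notes that test results should not decide delivery in isolation; and the ratio is known to clinicians only if available. Women delivered for confirmed pre-eclampsia may well receive intervention whatever the ratio showed. Each point argues for weaker steering than 70% versus 20%. With few cases per stratum, an artefact of 1 to 2 points would be lost in noise.

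A reader might further infer that a new GlyFn cut-off will be fitted in every subgroup, since all analyses are repeated. The article points the other way: it derives thresholds from the study cohort and refers to the cut-off in the singular.

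What survives is narrower. The point is not missing detail: the article itself names this stratifier and commits all analyses to it, and nothing in it excludes care that follows the disclosed result. Acknowledging intervention bias in general does not deal with this conditioning, and stratifying on interventions adds a selection effect instead of removing that bias.

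**Conclusion.** The concern holds conditionally. If interventions include care given after the first paired sample, the subgroup conditions on a consequence of the ratio but not of GlyFn, and equally accurate tests can show false differences of opposite sign in the two strata. The direction follows from the design, provided that care responds to a positive ratio as the article implies. The size rests on assumed steering, sensitivity and correlation: about 1 to 2 points at the weak setting, and 10 and 17 points at the strong setting with independent errors. So the artefact may fall well inside the 5% margin or well outside it. It is exactly zero if only pre-test treatment is meant. The full-cohort primary comparison is not affected; the risk is confined to a secondary table that could be misread as showing where the test works. The change is worth making because the wording as it stands allows the biased analysis.

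**What to change.** Remove interventions as a stratifier for the test-accuracy comparison, or restrict it in one clause to treatment already in place before the first paired sample. Report care after that sample descriptively only. State that the other subgroups are defined by status at the first paired sample, and that the single cohort-derived GlyFn cut-off applies in each. This is a wording change to the analysis section that needs no new data and does not alter care. The downside is at most one fewer subgroup table.
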